## Abstract

**Background:**

Although several studies have been conducted and several articles have been published on India's new clinical trial regulations, very few have examined the views of investigators and ethics board members regarding modifications to the previous regulations. Overall, they have neglected to find out the opinions of other relevant professionals, such as research assistants, coordinators, associates, and managers. To our knowledge, no study has yet investigated the awareness and opinions of Indian research professionals on the new 2019 regulations.

**Objective:**

This study aims to describe the awareness and opinions of Indian research professionals on the new drug and clinical trial regulations.

**Results:**

The survey was opened in July 2019. Enrollment has already started and will be completed in three months. The results calculations are expected to begin in October 2019.

**Conclusions:**

The results of the survey are expected to represent the views of research professionals on the new regulations that will support the development of clinical research and the pharmaceutical industry in India. These regulations are expected to help advance clinical trials, help with the approval of new drugs, and enhance ethical norms in the country.

**International Registered Report Identifier (IRRID):**

PRR1-10.2196/14744

## Introduction

### Background

In India, the clinical trials industry has exemplified rapid growth in the last few years, driven by economic globalization, and is thus one of the most promising economic sectors in the country [1]. This rapid growth of clinical trials may be attributed to the outsourcing of clinical trials to India by various multinational pharmaceutical organizations [2]. Furthermore, the availability of infrastructure, such as comprehensive treatment, a broad spectrum of prevalent disorders, ethnic variation, English-speaking health care specialists, and medical and information technology, provides proper conditions for conducting clinical trials in the country [2]. However, reports of irregularities in the administration of clinical trials has overshadowed the flourishing of the industry [2,3]. These ethical violations in the industry have exposed loopholes in the regulatory system, which has led to it struggling to oversee clinical trials effectively [4,5].

Due to this, the loopholes of the regulatory system were amended in 2016 by Indian authorities to strengthen the regulatory mechanisms for reviewing clinical trials. These amendments were issued based on a high level of scrutiny, significant media attention [6], the involvement of non-governmental organizations [3], hearings in the Supreme Court, and the recommendations of an expert committee [7]. Details of these three back-to-back amendments and their associated challenges have been summarized elsewhere [8-11]. Furthermore, two pilot studies have detailed the knowledge of investigators and members of ethics boards regarding the impact of these regulations [12,13].

Recently, new regulations were issued in 2019 [14], which involved amending the 2016 regulations [8] to bring further changes in the clinical research sector. These rules have focused on clarifying the terms of clinical trials of new drugs and phase IV trials, and of clarifying post-trial access to new drugs, clinical trial approval validity, equality, compensation, and monitoring, which have all been described elsewhere [15]. To our knowledge, no study has thus far described research professionals’ awareness and opinions regarding these new rules and regulations.

### Objectives

The purpose of this survey is to describe the awareness and opinions of research professionals on the new drug and clinical trials regulations.

### Hypothesis

We hypothesize that most Indian research professionals will be aware of, will welcome new changes to, and will agree that these new changes will speed up clinical trials, new drug approval, and improve ethical standards for clinical trials in the country. Also, they will aid with the expansion of clinical research and the pharmaceutical industry in India.

## Methods

### Overview

The methodology used in this survey is based on previous studies [16-18], and on the Checklist for Reporting Results of Internet E-Surveys (CHERRIES) [19].

### Ethics

The Institutional ethics committee was notified about the intended survey and excused from the review. This study does not require the informed consent of participants because this is an observational survey involving no risk or minimal risk to participants [20].

### Design

A cross-sectional, online survey design will be adopted to collect the data. No data which directly identifies any of the participants will be collected, but data that indirectly identifies participants, such as demographic information (eg, age, gender), will be collected. Mean, or range will be used to represent age, and counts/percentages will be used to show gender. We will select participants from different sources, including databases (eg, Clinical Trial Registry India, Indian Society Clinical Research, and the Central Drugs Standard Control Organization), personal networks, hospitals, institutions, and LinkedIn.

### Participant Eligibility Criteria

Those who are eligible to take part in this survey include research professionals. For this study, a research professional is defined as research investigators, members of ethics committees, assistants, coordinators, associates, and managers who have engaged in clinical trials in India. The number of target participants for this survey will be 80-100. Participants will be chosen randomly to avoid any selection bias.

### Data Collection

Validated questionnaires were selected from previous studies [12,13] and obtained from the respective authors or journals with their approval for use in the present project. Each questionnaire was developed using the form function in Google docs, which is a widely used and free survey tool [21]. A link was generated to enable participants to take the survey online [22]. The Google form feature of a limit of one respondent per email (respondents will be required to sign into Google) was enabled to prevent multiple entries from the same people. The “required to answer” feature was also enabled for each question, except for the following question: “If you are a member of the ethics committee, what is your role?”

The survey was announced on LinkedIn [23]. An email or message with a website link was sent to participants on LinkedIn to request that they complete the online, self-administered questionnaire. Participants' participation in this survey is entirely voluntary and anonymous. Therefore, it does not require participants to provide a name or any other identifying information, except for age and gender. Email reminders will be sent to all the participants to ensure the maximum possible number of responses. Respondents will be able to review and change their answers before clicking on the submit button at the end of the form. All the responses will be accessible by only the study investigator.

### Outcome

The outcome of this will be an enhanced understanding of research professionals’ awareness and opinions of the new clinical trials rules that came into effect in 2019.

### Statistical Analysis

Descriptive statistics will be estimated for continuous variables, whereas counts and percentages will be shown for categorical parameters. These data will be utilized to describe the awareness and opinions of the participants. *Post hoc* tests, such as the independent one-tailed *t* test and chi-square test, will be employed to test the significance of continuous and dichotomized parameters, respectively. Missing data will be explored in future studies, as appropriate. Results will be presented through graphs or tables. An analysis will be carried out utilizing SAS version 9.2 for Windows (SAS Corporation Inc, North Carolina, USA).

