## Discussion

### Primary Findings

This study, using a Web-based, online, open survey, aims to investigate the awareness and opinions of Indian research professionals who have engaged in clinical trials regarding the new rules put into place in 2019. It is crucial to understand the awareness and opinions of Indian research professionals, as they act as communicators and are a bridge between sponsors and patients. Therefore, understanding the awareness levels and opinions of these research professionals is crucial to determine whether clinical trials are being conducted per the new rules. Furthermore, considering the new directives, these professionals play a crucial role in addressing and reporting unethical clinical trials on vulnerable populations in India.

This open survey will be conducted online, so it will not be necessary to meet participants at any point physically. The survey will need about 10 minutes to complete. Participants will be able to take the survey on their mobile devices or their computers. Participation in this survey will be voluntary and anonymous, which is expected to boost the response rate.

The findings will expand the current knowledge base regarding the awareness and opinions of various Indian research professionals on the new clinical trial regulations, and allow for comparison to the findings of previous studies. Some professionals may have a higher level of awareness of the regulation now or may even have changed their perspectives regarding the recent amendments to Schedule Y of the Drug and Cosmetic Act.

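### A one-tailed t test is named for post hoc comparisons although no direction between groups is stated; if the tail follows the data, the false-positive rate is twice the nominal level

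*Protocol article*

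**What the plan says.** The Statistical Analysis section first plans descriptive statistics, counts and percentages. It then adds tests labelled post hoc, "such as the independent one-tailed *t* test and chi-square test, will be employed to test the significance of continuous and dichotomized parameters", the t test for the former and chi-square for the latter. It names no groups, no variables, no direction, no significance level and no reason for a single tail.

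Three other places bear on direction:

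- **Objectives:** "The purpose of this survey is to describe the awareness and opinions of research professionals on the new drug and clinical trials regulations". This is descriptive, with no contrast between groups.
- **Hypothesis:** "We hypothesize that most Indian research professionals will be aware of, will welcome new changes to, and will agree" that the changes will have several benefits. This is a statement about a majority of the whole sample.
- **Discussion, Primary Findings:** "Some professionals may have a higher level of awareness of the regulation now or may even have changed their perspectives". This is a possibility, contrasting now with earlier.

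On size, Participant Eligibility Criteria states: "The number of target participants for this survey will be 80-100".

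**The concern.** A one-tailed test puts the whole error allowance on one side. That is legitimate when the side was chosen in advance and a difference the other way would be treated as no finding. Here the test compares the means of two independent groups, yet nothing in the article says which group should score higher, and the tests are called post hoc. The analyst is therefore free to look at the two means and test in the direction in which they differ.

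At stake is the credibility of any t-test result reported as significant. The threshold would be easier to pass than its label suggests, and easier than the one applied to dichotomized parameters by the chi-square test.

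**Working it through.** The article gives no significance level, power or sample-size calculation, so there is no figure of its own to reproduce.

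**Inputs**

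- Test: independent t test, one-tailed (Statistical Analysis).
- Total sample: N = 80 to 100 (Participant Eligibility Criteria), so df = N − 2 = 78 to 98.
- Group split: not given. Assumed 1:1, with 1:3 as a check.
- Nominal level a: not given. Assumed 0.05, with 0.01 to 0.10 shown.

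**Step 1. Is a direction fixed anywhere?** The hypothesis that most respondents are aware concerns a proportion in one sample. It cannot supply the tail for a comparison of two group means. The Discussion remark is conditional, its second half (changed perspectives) has no direction, and the Statistical Analysis section does not refer to it. No direction between groups is fixed.

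**Step 2. Error rate if the tail follows the data.** Under the null hypothesis T is symmetric about zero. Testing in the observed direction rejects whenever |T| exceeds the one-tailed critical value:

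P(|T| > t[1−a, df]) = a + a = 2a

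| Nominal a | Direction fixed beforehand | Tail follows the data |
|---|---|---|
| 0.01 | 0.01 | 0.02 |
| 0.025 | 0.025 | 0.05 |
| 0.05 | 0.05 | 0.10 |
| 0.10 | 0.10 | 0.20 |

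The result does not depend on N or on the split. Simulation (100,000 null data sets per setting; N = 80 and 100; splits 1:1 and 1:3) agrees at a = 0.05: 0.098 to 0.101 when the tail follows the data, and 0.049 to 0.050 when the direction is fixed.

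**Step 3. The two-sided alternative at a = 0.05.**

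| N | One-tailed critical t | Two-sided critical \|t\| |
|---|---|---|
| 80 | 1.665 | 1.991 |
| 100 | 1.661 | 1.984 |

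The simulated two-sided false-positive rate is 0.049 to 0.050, whichever way the means differ.

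**Step 4. Comparison with the chi-square test.** With 1 degree of freedom at 0.05, the chi-square critical value is 3.841 = 1.960², the two-sided normal threshold squared. The matching one-tailed threshold is 1.645² = 2.706. At the same nominal level, a continuous parameter is held to the lower bar.

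**Step 5. Power given up by the two-sided test.** Normal approximation, a = 0.05, equal groups, standardised differences of 0.3 and 0.5 assumed for illustration, with the true effect in the tested direction:

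| Per group | Difference | One-tailed | Two-sided | Loss |
|---|---|---|---|---|
| 40 | 0.3 | 0.381 | 0.268 | 0.113 |
| 40 | 0.5 | 0.723 | 0.609 | 0.114 |
| 50 | 0.3 | 0.442 | 0.323 | 0.119 |
| 50 | 0.5 | 0.804 | 0.705 | 0.099 |

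**The case against.** **The article does not say that the tail will be chosen from the data.** This stands. Calling a test post hoc shows that it is secondary, not how its side is picked, and an analysis plan that is not shown could fix a direction for each comparison. A reader might infer that the real error rate is double. The documents support only that it is double if the tail follows the data, and nominal otherwise.

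**The Discussion may supply a direction.** It foresees comparison with previous studies and says awareness may be higher now. Respondents to an earlier survey and to this one could be independent samples. This is the best available source of a direction, but it is weak: it is worded as a possibility, covers awareness only, and is never linked to the t test.

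**The chi-square contrast can be pushed too far.** A reader might infer that the same question would be analysed both as continuous and as dichotomized, with conflicting answers. The article assigns each test to its own type of parameter and does not say that any item is analysed twice. What stands is the difference in standard between the two types.

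**Multiplicity is a separate matter.** A reader might extend the argument to a family-wise error rate over many comparisons. The article gives no number of comparisons, and such inflation would arise with two-sided tests as well.

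**Little depends on this test.** This largely stands. The objective is descriptive and the tests are introduced as examples. But the one-tailed t test is the only test named for continuous parameters, so the choice is explicit, not a detail left open.

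**Conclusion.** The point holds as a badly fixed choice: a one-tailed two-sample test is named for post hoc comparisons, and no direction between groups is stated anywhere in the article to justify the tail.

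The consequence is conditional. The factor of two applies at every nominal level, but only if the side is taken from the observed means. The figure of 0.10 rests further on an assumed level of 0.05. The unequal standard against the chi-square test does not depend on how the tail is picked; it follows from the two tests as named, used at a common nominal level.

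A reader might take this as a threat to the study's main conclusions. The documents do not support that: awareness and opinions are to be described by counts and percentages, and whether most respondents are aware is answered by a percentage, which sidedness does not touch. It should be fixed, but nothing central turns on it.

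**What to change.** In the Statistical Analysis section, replace the one-tailed independent t test with a *two-sided independent t test*, and say that these between-group comparisons are exploratory. This holds the error rate at nominal whichever way the means differ and puts the t test on the same footing as the chi-square test.

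If a one-tailed test is really wanted for a particular comparison, the alternative is to state the two groups, the variable, the expected direction and the reason for it before the responses are examined.

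The edit is one sentence. The price is nominal power: about 10 to 12 percentage points in the illustrative settings above, relative to a one-tailed test pointed the right way. That is acceptable for exploratory comparisons, which the descriptive objective does not rely on.

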## Results

The enrollment of Indian research professionals will begin from multiple sources in July 2019 and is expected to end in November 2019. The results evaluations are expected to start in October 2019. The survey questionnaires being used in this project were previously validated by other studies [12,24], and approval was obtained for their reuse. The demographic characters of the respondents, such as age, gender, and region in India, will be presented in a table. The awareness and opinions of the respondents will be summarized in tables and illustrated as a pie chart.

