### Limitations

Nonetheless, this survey has some limitations. First, the survey will be taken by only a specific sample within the population. Therefore, the results cannot be generalizable to the whole population of India. Second, self-administered questionnaires may introduce some level of social desirability bias. Finally, the surveys are limited by their cross-sectional design, which allows us to determine the association but not causality.

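### Undefined post hoc tests are planned to declare significance beside a purely descriptive objective; the comparisons should be labelled exploratory and all of them reported as estimates with confidence intervals

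*Protocol article*

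**What the plan says.** In the protocol article, the Objectives section is descriptive: "The purpose of this survey is to describe the awareness and opinions of research professionals on the new drug and clinical trials regulations". Statistical Analysis begins in the same vein, with summary statistics, counts and percentages, and states: "These data will be utilized to describe the awareness and opinions of the participants".

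The same section then adds significance testing, labelled *post hoc*. The examples it names are the "independent one-tailed *t* test and chi-square test". According to the article, these "will be employed to test the significance of continuous and dichotomized parameters, respectively". The list is introduced by *such as*, so it is open. The parameters, the groups, the significance level and the direction of the one-tailed test are not given.

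Two other places bear on how many tests there might be:

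- The Hypothesis section makes several statements of equal rank about what most professionals think, among them that they "will agree that these new changes will speed up clinical trials, new drug approval, and improve ethical standards".
- The Results section mentions respondent characteristics, but only for description: "The demographic characters of the respondents, such as age, gender, and region in India, will be presented in a table".

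**The concern.** An independent t test needs two groups and a chi-square test needs a cross-classification or a reference value, so the planned tests imply comparisons. The article does not leave their choice open for another document to fill. It calls them *post hoc*, which means chosen once the data are in hand, and in the same sentence gives them the job of establishing significance. These two statements do not fit together. A p-value from a comparison selected after inspection does not carry its nominal error rate, and readers cannot tell how many comparisons were tried.

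What is at stake is selective reporting. With 80 to 100 respondents (Participant Eligibility Criteria), a few significant differences in awareness or opinion could be published when nothing is truly associated. The problem would remain if every test were two-sided.

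**Working it through.** The article gives no alpha, power, effect size or number of tests, so it has no figure of its own to reproduce. The calculation shows what the stated rule permits over a range of assumptions.

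**Inputs**

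- Alpha: assumed 0.05 per test, two-sided, so the critical value is c = 1.96.
- Number of tests m: not stated; assumed 2, 6 and 18. Six matches a count of the constructs in the Hypothesis section (aware, welcome, faster trials, faster approval, better ethics, industry growth). Eighteen would be those six crossed with age, gender and region, that is 6 × 3. The article never says that they will be crossed, so this is an illustration only.
- Common correlation ρ between test statistics: assumed 0, 0.5 and 0.8.
- All null hypotheses true.

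**Step 1: independent tests.** P(at least one false positive) = 1 − (1 − 0.05)^m.

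- m = 2: 1 − 0.95² = 0.0975
- m = 6: 1 − 0.95⁶ = 0.265
- m = 18: 1 − 0.95¹⁸ = 0.603

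The probability first exceeds one half at m = 14: 1 − 0.95¹³ = 0.487 and 1 − 0.95¹⁴ = 0.512.

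**Step 2: correlated tests.** For equicorrelated normal statistics,

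P = 1 − ∫ φ(u) · [Φ((c − √ρ·u)/√(1−ρ)) − Φ((−c − √ρ·u)/√(1−ρ))]^m du.

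| m | ρ = 0 | ρ = 0.5 | ρ = 0.8 |
|---|---|---|---|
| 2 | 0.10 | 0.09 | 0.08 |
| 6 | 0.27 (0.26 by integration) | 0.21 | 0.14 |
| 18 | 0.60 | 0.40 | 0.22 |

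The 0.27 is a simulated value (0.266); the exact value is 0.265. If the six items correlate at 0.5 within each of three groupings and the groupings are independent, 18 tests give 0.50.

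**Step 3: what formal adjustment would cost.** Take a comparison of 50% with 70% in two equal groups of n, using power = Φ((0.20 − z·SE₀)/SE₁), with SE₀ = √(2 × 0.6 × 0.4/n) and SE₁ = √((0.25 + 0.21)/n). The rates and the equal split are assumptions. Bonferroni over 20 tests gives 0.05/20 = 0.0025 per test.

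- 80 respondents (n = 40): power falls from 44.5% (z = 1.96) to 11.1% (z = 3.02).
- 100 respondents (n = 50): power falls from 53.3% to 15.8%.

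Mandatory adjustment would leave little power for a difference of this size, which argues for estimation rather than adjusted testing.

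**The case against.** The case against has four parts.

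1. *A condensed article may leave contrasts and multiplicity rules to a fuller document.* This stands for their bare absence, which is not the point here. What remains is what the article does state: the tests are *post hoc* and are used to establish significance. A pre-specified list elsewhere would conflict with that label.

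2. *The family of tests is inferred.* This stands. The Results section only tabulates age, gender and region, the Hypothesis section contains no between-group contrast, and Statistical Analysis speaks only of parameters. The figures for 6 and 18 tests are therefore illustrations, not counts taken from the plan.

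3. *No confirmatory claim rests on these tests.* This largely stands. The objective and main analysis are descriptive, there is no decision rule, and *post hoc* hints at secondary status. Formal family-wise control is therefore not obligatory. The hint does not settle the matter, because the same sentence still sets out to test significance.

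4. *The Limitations wording is harmless.* This stands. A reader might take the remark that the design is one "which allows us to determine the association but not causality" as a promise that the tests will establish associations. It is a general caveat about cross-sectional designs, is not tied to the planned tests, and needs no change.

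**Conclusion.** The point holds as a badly fixed analysis sentence. Open-ended *post hoc* tests are given the task of establishing significance in a study whose objective is to describe, so differences selected after the data are seen could be declared significant at full alpha.

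On size, even two tests raise the chance of a false positive to about 0.08 to 0.10 from a nominal 0.05. More tests raise it further, to between 0.22 and 0.60 at 18. These figures assume a two-sided 5% level, no true differences and the stated correlations.

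A reader might infer that chance findings are likely. The article does not support that: the number of tests is unknown, the figure for 18 tests at a correlation of 0.5 is 0.40, and one half is passed only from 14 tests if they are independent. *Substantial chance* is the accurate description. A reader might also infer that the plan needs compulsory multiplicity adjustment; with a descriptive objective it does not. The correction is worth making because it is nearly free and limits selective reporting.

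**What to change.** In Statistical Analysis only, replace the sentence on *post hoc* tests with:

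> Group comparisons are exploratory; all comparisons performed will be reported as differences in means or proportions with 95% confidence intervals, and no claim of statistical significance will be made from unadjusted p-values.

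A Holm adjustment over all comparisons performed is optional, for use if the authors wish to declare significance. The Limitations section can stay as it is.

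The cost is one sentence, with no extra respondents and no change to the questionnaire. The downside is that fewer differences can be called significant. Unadjusted intervals do not remove multiplicity for a reader who only checks whether they exclude zero, but reporting every comparison lets that reader see how many were made.
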